### Outcome measures

#### Primary outcomes: feasibility and acceptability

Feasibility and acceptability were defined as the primary outcomes of the study. These were evaluated using the following:
Structured student and faculty questionnaires assessing perceived usefulness, clarity, workload, and trust in the AI-assisted process;System usage metrics, including completion rates and interaction frequency; andOpen-ended qualitative feedback to capture implementation barriers and facilitators.Survey instruments used Likert-scale items supplemented by free-text responses.

#### Secondary outcomes: analytic agreement

Secondary outcomes focused on exploratory agreement between AI-derived competency clusters and faculty assessment outcomes. Agreement was examined using the following:
Confusion matrices comparing AI cluster membership with faculty-assigned performance categories;Percentage agreement; andCohen's Kappa, reported with 95% confidence intervals.These analyses were conducted to explore alignment patterns rather than to claim validation or diagnostic performance.

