### AI-assisted assessment framework

The AI component consisted of an unsupervised machine learning–based clustering module designed to group students according to multidimensional performance indicators derived from assessment artifacts (e.g., rubric scores, task completion metrics, and structured feedback variables). No outcome labels or performance categories were predefined, and the algorithm did not generate pass/fail or diagnostic classifications. Clustering outputs were interpreted as exploratory competency profiles intended to support sensemaking and reflection, rather than automated judgment. The AI system functioned strictly as a decision-support tool, with all summative decisions retained by faculty.

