### Data processing

This pilot feasibility study focuses on a single group of students from the Bachelor Program at College of Health Sciences (CoHS), GMU, with a minimum sample size of 40 participants to assess the feasibility and acceptability of the approach. Given the pilot sample size (*n*=40), model evaluation will use repeated stratified k-fold cross-validation (or leave-one-out CV) and bootstrap confidence intervals to reduce instability from fixed splits. A pre–post analysis will be conducted to evaluate the significance of differences in the occurrence of high-risk students at each stage of data collection (across three time points). The third assessment point will be their final score and passing percentage. Subsequently, this study may be expanded to a larger sample size using a cluster-randomized group study design. The project will utilize Python and related libraries.

Additional automated alerts and academic advice generated by AI will be thoroughly cross-verified by the investigators with respect to the target students and mentors. In parallel, the investigators will manually analyze student performance using data from the three designated time points [human-in-the-loop governance (mentor approval and escalation)]. This process will allow the investigators to confirm the integrity, accuracy, and functionality of the newly proposed AI mentorship model. A survey will also be conducted among the targeted students and faculty to assess their responses, success rates, and the accuracy of the proposed AI co-mentoring model in tracking academic progress. The present study is designed to use quantitative data, while qualitative data from the survey will be used for validation purposes. Figure 1 provides an overview of the intended workflow in the form of a flowchart.

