#### Analysis of secondary outcomes

Secondary analyses focused on exploratory agreement between AI-derived student clusters and faculty assessments. AI outputs were treated as unsupervised groupings, without prespecified performance labels. Agreement between AI cluster membership and faculty-assigned performance categories was examined using (1) confusion matrices, (2) percentage agreement, and (3) Cohen's Kappa, with 95% confidence intervals

Given the limited sample size, Kappa values were interpreted cautiously, emphasizing direction and magnitude rather than threshold-based validity claims.

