#### Resampling and stability assessment

To assess the stability of observed agreement patterns, resampling-based techniques were employed where applicable. Repeated stratified k-fold cross-validation was used to examine the consistency of clustering–assessment alignment across different data partitions. These procedures were not intended to optimize model performance but to evaluate robustness under data perturbation. The results from resampling analyses were summarized descriptively, and variability across folds was reported to reflect uncertainty inherent in small-sample modeling.

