#### Sample size and power considerations

Formal power calculations were not performed, as the study was not designed to test hypotheses or estimate diagnostic performance with precision. Instead, the sample size was determined by cohort availability, consistent with pilot-study methodology.

Confidence intervals were reported for agreement statistics to provide transparency regarding sampling variability and interpretability limits. All findings are therefore considered hypothesis-generating and intended to inform the design of larger, adequately powered confirmatory studies.

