#### Interpretation framework

Analytic results were interpreted within a decision-support paradigm, recognizing faculty assessment as the reference standard and AI outputs as supplementary insights. Statistical findings were used to characterize alignment patterns rather than to adjudicate correctness or automate evaluative decisions.

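### Kappa and percentage agreement are computed between unlabelled clusters and faculty categories, with no rule stated that links one to the other

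*Protocol article*

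**What the plan says.** Under Secondary outcomes: analytic agreement, the protocol article lists "Confusion matrices comparing AI cluster membership with faculty-assigned performance categories", then percentage agreement and Cohen's kappa with 95% confidence intervals. Analysis of secondary outcomes repeats this: "Agreement between AI cluster membership and faculty-assigned performance categories was examined using (1) confusion matrices, (2) percentage agreement, and (3) Cohen's Kappa".

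The same section describes the AI side of the table: "AI outputs were treated as unsupervised groupings, without prespecified performance labels". AI-assisted assessment framework agrees: "No outcome labels or performance categories were predefined, and the algorithm did not generate pass/fail or diagnostic classifications". Interpretation framework describes the analysis as "recognizing faculty assessment as the reference standard and AI outputs as supplementary insights".

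Resampling and stability assessment builds on the same comparison: "Repeated stratified k-fold cross-validation was used to examine the consistency of clustering–assessment alignment across different data partitions".

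The sample is about 40 students, set by cohort availability. The analysis is declared exploratory, and kappa is to be read cautiously for its sign and size and not against a threshold.

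**The concern.** Percentage agreement is the share of students on the diagonal of a square table whose rows and columns carry the same category names. Kappa corrects that share for chance. A clustering algorithm returns groups numbered arbitrarily, so the table has a meaningful diagonal only after someone decides which cluster stands for which faculty category. If the two sides have different numbers of groups, there is no diagonal at all.

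The article chooses statistics that need this link and also says that the groups carry no performance labels. This goes beyond a detail left out of a condensed text: the stated nature of the AI output and the stated statistic do not fit together. At stake is whether the reported kappa can be interpreted, since the numbering alone can set the sign and size that the plan intends to read.

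**Working it through.** **Inputs.** n = 40 (Data processing). The article gives no number of clusters, number of faculty categories, category shares or target kappa. There is therefore no figure of its own to reproduce, and the group numbers and shares below are assumptions.

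**Formula.** kappa = (po - pe)/(1 - pe), where po is the diagonal share and pe is the sum over categories of (row total x column total)/n².

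**Step 1: arbitrary numbering, perfect clusters.** Suppose the clusters reproduce three faculty categories of 20, 12 and 8 students exactly. Only the cluster numbers are permuted.

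| Label order | po | pe | kappa |
|---|---|---|---|
| all correct | 40/40 = 1.00 | (400+144+64)/1600 = 0.38 | 1.00 |
| groups 2 and 3 swapped | 20/40 = 0.50 | (400+96+96)/1600 = 0.37 | 0.13/0.63 = 0.21 |
| groups 1 and 3 swapped | 12/40 = 0.30 | (160+144+160)/1600 = 0.29 | 0.01/0.71 = 0.01 |
| groups 1 and 2 swapped | 8/40 = 0.20 | (240+240+64)/1600 = 0.34 | -0.14/0.66 = -0.21 |
| either rotation (two orders) | 0 | (240+96+160)/1600 = 0.31 | -0.31/0.69 = -0.45 |

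The partition is the same in every row. An imperfect table behaves likewise: with rows (16, 3, 1), (2, 9, 1), (0, 2, 6), kappa runs from 0.64 to -0.33 and agreement from 77.5% to 10.0% over the six orders.

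**Step 2: matching afterwards, no true association.** Simulated data sets had n = 40 and clusters independent of faculty categories, so true kappa is 0. The cluster-to-category match with the highest agreement was taken. Shares are the same on both sides.

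| Groups and shares | Mean kappa, mapping fixed in advance | Mean kappa, best match | 95th percentile, best match |
|---|---|---|---|
| 2, 50/50 | 0.00 | 0.12 | 0.30 |
| 2, 70/30 | 0.00 | 0.05 | 0.28 |
| 3, equal | 0.00 | 0.15 | 0.28 |
| 3, 50/30/20 | 0.00 | 0.12 | 0.26 |
| 4, equal | 0.00 | 0.17 | 0.27 |
| 4, 40/30/20/10 | 0.00 | 0.14 | 0.25 |

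Mean agreement rises too, from 33% to 44% with three equal groups and from 25% to 38% with four. Letting the shares differ between the two sides (40/35/25 against 50/30/20; four equal groups against 40/30/15/15) gives mean kappas of about 0.13 and 0.16, within the same range.

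**Step 3: matching afterwards, real association.** Three groups, shares 50/30/20, n = 40.

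| True kappa | Mean, correct fixed mapping | Mean, best match | Random numbering: mean (SD) |
|---|---|---|---|
| 0.3 | 0.295 | 0.302 | 0.01 (0.18) |
| 0.6 | 0.595 | 0.595 | 0.01 (0.31) |
| 0.8 | 0.796 | 0.796 | 0.02 (0.40) |

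Matching bias has nearly gone at a true kappa of 0.3. Random numbering wipes out the signal whatever the true agreement.

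**Step 4: the stability check.** Cluster numbers can switch from one partition to the next. Fold-to-fold variability in kappa would then mix real instability with renumbering, unless one mapping rule is applied within every fold.

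**The case against.** The strongest reply is that a third route exists. Clusters can be mapped by a rule that ignores the faculty ratings, such as ordering them by mean score, and kappa is then unbiased (the fixed-mapping columns above). The article does not exclude this. Its remark about missing labels may describe only the input to the algorithm, Software and reproducibility says settings were fixed before analysis, and Table 1 shows the unsupervised system producing High and Medium levels. A condensed article might leave the mapping to a fuller document.

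Part of this stands. A reader might infer that the reported kappa must be either meaningless or inflated; the documents do not support that, because a blind mapping may have been intended. But neither the statement on settings nor Table 1 gives a rule, and Table 1 sits awkwardly with the assertion that no performance categories were predefined. The text as it stands still applies a label-dependent statistic to groups it calls unlabelled.

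Three further limits are fair.

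- A reader might take this kappa to be the only quantitative evidence on the AI. It is not: the article also plans usage metrics and questionnaires, cross-validated model evaluation, a pre-post analysis of high-risk students, and accuracy and precision for the supervised models.
- A reader might want to say how often the 95% interval would wrongly exclude zero after matching. That depends on a standard error the article does not name. Data processing mentions bootstrap intervals for model evaluation, so no particular rate can be attributed to the plan.
- The outcome is secondary, with no hypothesis test and explicit disclaimers; as the article puts it, "Formal power calculations were not performed, as the study was not designed to test hypotheses or estimate diagnostic performance with precision". That limits the consequence, but it does not make a number interpretable when its sign can turn on numbering.

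**Conclusion.** The point holds: percentage agreement and kappa are applied to clusters that the article says have no performance labels, with no mapping and no equality of group numbers stated. Under arbitrary numbering, the result for one perfect partition of 40 ranges from 1.00 to -0.45. Under best matching after the fact, the upward bias is about 0.12 to 0.17 for three or four groups with no true association, about 0.05 to 0.12 for two groups, and negligible from a true kappa of about 0.3 in the three-group scenario. It would therefore be wrong to call a matched kappa inflated in general; the problem is telling weak agreement from none, which matters at this sample size. The ranges rest on assumed group numbers and shares. The resampling check inherits the fault. Because the outcome is secondary and exploratory, this is something the plan should fix, not a defect that invalidates the study.

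**What to change.** For clusters against faculty categories, choose one of two routes and write it into the analysis section before the data are analysed.

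1. Replace kappa and percentage agreement with a chance-corrected, label-invariant index, either the adjusted Rand index or adjusted mutual information. Give a permutation reference distribution and a student-level bootstrap interval that re-runs the clustering in each replicate. The confusion matrix can stay as a description.
2. Keep kappa and percentage agreement, but fix beforehand the number of clusters (equal to the number of faculty categories) and a mapping made without the faculty ratings, for example ranking clusters by mean summative score. Apply that rule within every fold and bootstrap replicate.

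Do not make uncorrected Cramér's V the headline index: under pure noise at n = 40 its mean is 0.21 with three groups and 0.27 with four. Use kappa for the rule-based or supervised risk category only if faculty rate on the same defined categories. The article does not define the faculty categories, and Table 2 gives no category for summative scores from 60% to 70%.

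The cost is a few sentences and a few lines of Python. The drawback of the first route is a less familiar index whose values will usually be lower than a matched kappa. The article places recruitment in Academic Year 2026, so the change can be made before analysis.

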### A sample risk assessment summary by a supervised AI system

A sample CHATGPT-4 automated risk report with a message generation layer [templated or large language model (LLM)-assisted drafting; student-specific academic counseling messages] is provided in the following (Supervised AI mentoring model):

Sample Automated Risk Report by AI (Based on Analysis of Academic Performance)

Dear Student,

Subject: Academic Progress/Student at Risk/Academic Counseling

Based on the latest academic performance evaluation for the course [Course Name – Course Code], you have been identified as at risk of not meeting the passing criteria, as your current performance falls below the required benchmark.

Your academic progress as of [Date] is summarized as follows:

Attendance: 80%

Class Test: 55%

Coursework: 65%

Midsemester Exam: 65%

Total Average Score: 61.67%

[Passing benchmark: You must achieve a minimum score of 65%.]

### Sample-automated unsupervised AI advice

The message generation layer (templated or LLM-assisted drafting) will be addressed to students and copied to mentors as a follow-up to the report.

Subject: Academic Performance Improvement Guidance

Dear Student,

You need to make significant improvements in your coursework and class tests to achieve the minimum benchmark of 65%–70%, as required by your program for successful course completion. Therefore, you must contact your course instructor immediately to seek further assistance and guidance.

The sooner you act on this report, the easier it will be to enhance your grades in the end-of-semester examination, overall course performance, and grade point average (GPA).

### Sample pedagogic AI-generated individualized academic advice/message generation layer (templated or LLM-assisted drafting) for both supervised and unsupervised models

#### Advisory—student performance

The student demonstrates moderate academic performance, with a total average of 61.7%, slightly below the required 65% pass mark. A key area for improvement is the Class Test component (55%), which indicates the need for strengthened conceptual understanding and test-taking strategies.

To improve this component and move past the 65% pass mark, consider the following:
Review key concepts regularly—Revisit lecture notes and learning materials to strengthen your understanding of core topics.Practice past papers or sample questions—This helps familiarize yourself with the question style and improve accuracy under time constraints.Clarify doubts early—Seek guidance from your course instructor or peers whenever you find a topic is unclear.Improve time management—Allocate sufficient time for each section during tests to ensure all questions are attempted.Focus on feedback—Analyze errors from previous tests to avoid repeating them in future assessments.Schedule a one-on-one mentoring session—Arrange a one-on-one meeting with your academic advisor for personalized guidance and study plans.To track individual student progress, similar reports will be generated at three different time points throughout the semester to analyze student improvement. To accomplish this, CHATGPT-4 will be programmed to notify both the mentor and the student if a student’s performance falls below the benchmark at the 5th and 10th weeks of each semester while the data are manually uploaded by the course coordinator for a given course. To support this, ChatGPT will send regular reminders over the following 2 weeks, encouraging students to take necessary actions to enhance their performance and meet the eligibility criteria for the end-semester examinations.

A sample risk identification category was developed to train ChatGPT-4 using structured prompts, enabling the text-generation service to draft mentoring messages from deidentified student performance summaries. An example of the risk profile generated by the unsupervised AI clustering system is presented in Tables 1 and 2. The authors plan to notify students of their cumulative grade point average (CGPA) scores as they transition from one semester to the next (Tables 3, 4) in order to keep the students informed of their academic achievements at each stage. This feature allows students to assess their progress, take proactive steps to improve, or maintain a strong CGPA.

**Table 1 T1:** Sample risk profile identified by an unsupervised AI system.

Area	Performance indicator	Risk level	Comments
Assignment submission	3/5 submitted	High	Two assignments are missing or late
Class attendance	62%	High	The following required 75% attendance
Practical test performance	45%	Medium	Needs improvement in learning demos of hands-on skills
Class test performance	68% average	Medium	Borderline performance
Participation and engagement	Low	High	Rarely engages in class discussions

**Table 2 T2:** Sample performance metrics of a supervised AI risk predictive model.

Assessment component 1 (20% weightage)			Assessment component 2 (20% weightage)			Assessment component 3 (25% weightage)			Analysis and risk identification	
Class test			Coursework			Midsemester Exam			Summative score 65 (excluding End-Semester Exam)	Risk category/performance appraisal
Score above 80% out of 20 (>16)	Score >70%but <80% out of 20 (>14)	Score <60% out of 20 (<12)	Score above 80% out of 20 (>16)	Score >70%but <80% out of 20 (>14)	Score <60% out of 20 (<12)	Score above 80% out of 25 (>20)	Score >70%but <80% out of 25 (>17.5)	Score <60% out of 25 (<15)	Score above 80% out of 65 (>52)	Above average^a^
									Score >70%but <80% out of 65 (>45.5)	Moderate risk: Meet your mentor for appropriate counseling^a^
									Score <60% out of 65 (<39)	High risk. Recommended for rigorous mentor advice, additional remedial measures, and follow-up^a^

^a^
Students will receive an automated checkpoint-based risk classification report at weeks 5 and 10 from chatbot.

**Table 3 T3:** Risk predictive model for the CGPA score.

Program/year/class	Evaluation component		Analysis and risk identification	
	GPA scores secured by students	GPA score conversion to percentage	Risk category	
			90–100	Satisfactory^a^
			85–<90	
			80–<85	Needs to improve in the grade/performance^a^
			75–<80	Moderate risk recommended for mentor advice^a^
			70–<75	
			Less than 70	High risk recommended for rigorous mentor advice, additional remedial measures, and follow-up^a^

^a^
Students will receive an automated checkpoint-based risk classification report at weeks 5 and 10 from chatbot.

**Table 4 T4:** Risk predictive model for assessing attendance and student regularity.

Evaluation component			Analysis and risk identification	
Attendance%			Predicted continuous assessment score 65%	Risk category
			Attendance >85%	Satisfactory^a^
			Attendance >80%<85%	Needs to improve in regularity^a^
			Attendance <80%	High risk suggestive of rigorous mentor counseling and follow-up^a^

^a^
Students will receive an automated checkpoint-based risk classification report at weeks 5 and 10 from chatbot.

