Previous risk prediction models developed by researchers relied on statistical analyses and calculations that were often too complex for faculty to easily understand and apply. Hence, the current study proposes to validate both supervised and unsupervised AI mentoring, using ChatGPT-4 and a predictive risk engine (rules + ML models) to recognize students at risk and provide them mentoring advice to help achieve their learning goals.

The AI Risk Identification Assistance System (AIAS) is conceptualized as a learning analytics early-warning system integrated with mentoring practice. The risk engine identifies students who may not meet the course benchmark (e.g., <65% continuous assessment), while the mentoring layer delivers self-regulated learning (SRL)-oriented prompts and facilitates timely human follow-up at weeks 5 and 10.

The novelty and originality of this project lie in its simplicity and practical application. Earlier studies utilized complex calculations and did not deeply explore how different AI applications align with specific pedagogical models or teaching strategies across disciplines and contexts. They focused on formulas to identify at-risk students and offered automated academic advice through AI. Furthermore, these studies often lacked regular follow-up phases to track student progress and did not test AI-driven mentoring models (14, 15).

Our proposed AI mentoring model is expected not only to recognize at-risk students based on their pedagogical assessment system but also to provide personalized advice to ensure their academic success. This will be achieved through regular automated reminders, risk reports, and academic advice generated by supervised and segmentation engines (unsupervised AI models). The role of the faculty is to simply upload the necessary data to the chatbot. The study will be conducted on students from Health Science at the College of Health Sciences, Gulf Medical University (GMU), UAE, for a semester.

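### Table 2 gives no risk category for continuous-assessment scores of 60–70% (or exactly 80%), although the 65% benchmark lies inside that gap

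*Protocol article*

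**What the plan says.** The Introduction gives the engine's purpose: "The risk engine identifies students who may not meet the course benchmark (e.g., <65% continuous assessment"). The sample report in the section on the supervised AI system repeats the figure to the student: "Passing benchmark: You must achieve a minimum score of 65"%. The sample unsupervised advice puts the benchmark at 65%–70%.

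Table 2, in the section headed Advisory—student performance, turns the summative score out of 65 into three categories:

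- "Score above 80% out of 65 (>52"): Above average
- "Score >70%but <80% out of 65 (>45.5"): Moderate risk
- "Score <60% out of 65 (<39"): High risk

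The same three cuts are printed for each component. For the class test and coursework the lowest is "Score <60% out of 20 (<12"). A footnote says that students will be sent an automated classification report at weeks 5 and 10.

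Table 4 does the same for attendance, with bands above 85%, "Attendance >80%<85"% and below 80%.

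The Data processing section plans a pre–post comparison, over three time points, of how often high-risk students occur.

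**The concern.** A classification rule should give every possible score exactly one category. Table 2 does not, and the hole lies where the engine has its main decision to make, on either side of the pass benchmark. Two rules in the same article then treat one student differently. Below 65% the student is at risk, but between 60% and 65% the graded table says nothing. Meanwhile a student ten points above the benchmark, at 75%, does receive a risk level.

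Two things depend on this. The first is the content of the graded report, since Table 6 ties the intensity and timing of support to the risk level. The second is the count of high-risk students across time points. The article does not say which rule defines high risk there, so a student in the gap could be handled differently by different raters, or at different checkpoints. The Software and reproducibility section says that parameter settings were fixed before analysis. For scores in this band, Table 2 as printed fixes nothing.

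**Working it through.** **1. Do the printed mark cut-offs reproduce?** Cut-off = percentage × maximum marks.

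| Maximum marks | 60% | 65% | 70% | 80% |
|---|---|---|---|---|
| 20 (class test, coursework) | 12 | 13 | 14 | 16 |
| 25 (midsemester exam) | 15 | 16.25 | 17.5 | 20 |
| 65 (summative) | 39 | 42.25 | 45.5 | 52 |

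All the 60%, 70% and 80% marks match Table 2. The same gap appears in all three components and in the total, each time with consistent marks, so it is not a flaw of text extraction. Table 3 uses touching bands (for example 80–<85), so gaps are not the authors' convention either.

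**2. Which scores have no category?** Applying >80, >70 and <80, and <60 as printed:

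| Score | Table 2 category | Below 65%? |
|---|---|---|
| 59.9% | High risk | yes |
| 60% | none | yes |
| 61.67% | none | yes |
| 64.9% | none | yes |
| 65% | none | no |
| 68% | none | no |
| 70% | none | no |
| 70.1% | Moderate risk | no |
| 80% | none | no |
| 80.1% | Above average | no |

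The uncategorised interval is 39 to 45.5 marks inclusive, plus exactly 52. The benchmark splits it: 39 to <42.25 marks fails with no category, and 42.25 to 45.5 meets the benchmark with no category.

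**3. The article's own sample student** has class test 55%, coursework 65%, midsemester 65% and attendance 80%.

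- Unweighted average: (55 + 65 + 65)/3 = 61.67%, the printed figure.
- With Table 2's marks: 0.55×20 + 0.65×20 + 0.65×25 = 11 + 13 + 16.25 = 40.25, and 40.25/65 = 61.92%.
- Either total falls in the gap. So do coursework (13 of 20, between 12 and 14) and midsemester (16.25 of 25, between 15 and 17.5).
- Attendance of exactly 80% fits no Table 4 band. Exactly 85% would not fit either.

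**4. How many students?** The article gives no score distribution. Assume normal scores with mean m and SD s. The share in 60–70% is Φ((70−m)/s) − Φ((60−m)/s), and the share in 60–<65% is Φ((65−m)/s) − Φ((60−m)/s). With s = 10:

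| m | 60–70% | of 40 | 60–<65% | of 40 |
|---|---|---|---|---|
| 65 | Φ(0.5) − Φ(−0.5) = 0.383 | 15.3 | Φ(0) − Φ(−0.5) = 0.191 | 7.7 |
| 70 | Φ(0) − Φ(−1) = 0.341 | 13.7 | Φ(−0.5) − Φ(−1) = 0.150 | 6.0 |
| 75 | Φ(−0.5) − Φ(−1.5) = 0.242 | 9.7 | Φ(−1) − Φ(−1.5) = 0.092 | 3.7 |

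Over the same means, the 60–70% share by the same formula is 0.468/0.394/0.236 with s = 8 and 0.323/0.298/0.233 with s = 12. The 60–<65% share is 0.234/0.160/0.075 and 0.162/0.136/0.097.

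**The case against.** A reader might infer that students who fail the benchmark go undetected. The article does not support that. Those below 60% are labelled High risk. The sample report tells its 61.67% student that they are at risk, and the Advisory section has mentor and student notified whenever performance is below the benchmark at weeks 5 and 10, with reminders over the following two weeks. Table 6 adds other triggers, such as non-submission and disengagement. Detection is provided for; a graded level is not.

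A reader might also infer that the gap damages the confusion matrix and kappa. The secondary-outcome sections cross-tabulate unsupervised clusters, without predefined labels, against faculty categories. Nothing says that Table 2 labels enter that matrix.

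Nor does the scale run backwards. The printed labels worsen as scores fall, and calling 75% Moderate risk may be a deliberate early-warning choice. The fault is incompleteness.

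Table 1 looks inconsistent with the other tables: its comment "The following required 75% attendance" sits beside Table 4's 80% cut, and a 45% practical score is rated Medium. But Table 1 is a sample output. A warning cut can sit above a requirement, and the practical test is not a Table 2 component. No clear contradiction follows.

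Table 2 is itself captioned as a sample, in a pilot whose primary outcomes are feasibility and acceptability. That lowers the stakes. It does not remove the point, because the footnote commits the study to sending students the classification, and no other graded rule for this score is given.

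Finally, if Table 2 alone defines high risk, the definition is clear (<39 marks) and students in the gap are simply not counted. That is fair. But the Data processing section does not say so, and the other tables use the same label with different cuts (below 70 for CGPA, below 80% for attendance).

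**Conclusion.** The point holds in a limited form. Table 2 as printed cannot classify scores of 60–70% or exactly 80%, and Table 4 cannot classify attendance of exactly 80% or 85%. This is certain from the page and needs no assumption. The 65% benchmark lies inside the gap, and the article's own example student falls into it on the total, two of three components and attendance.

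The consequence is that students at 60–<65% are at risk under one rule and ungraded under the other, and that their place in the high-risk count is not settled. They would still receive the below-benchmark notice, and neither the primary outcomes nor the cluster agreement analysis is shown to be affected.

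The size is only indicative. With normal scores, SD 10 and a mean of 65–75%, about 24–38% of the cohort (10 to 15 of 40) would have no Table 2 category, but only about 9–19% (4 to 8 of 40) would also be below the benchmark. With SD between 8 and 12 these ranges widen to about 23–47% and 8–23%.

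**What to change.** Before the week 5 checkpoint:

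- Make the Table 2 bands contiguous and exhaustive, and state which limits are inclusive, for the components as well as the total.
- Reconcile the bands with the 65% benchmark so that every score below it carries an at-risk level. The course team chooses the labels.
- Close Table 4 at 80% and 85% in the same way.
- State in the Data processing section which band or bands count as high risk in the comparison across time points.
- Keep the faculty rating independent of the AI label. Deriving both from one score ladder would push agreement towards 1 by construction and would not fit the label-free clustering.

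The cost is a rewording of two tables, one sentence in Data processing and matching changes to the prompts. No extra data are needed. A few more students may be given a graded risk label. The timing matters because bands completed after scores are seen would be post hoc.
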